## Methods

### Study Design

The study will track changes in smell and taste with COVID-19 infection using a prospective longitudinal, case-control study design. Participants will be recruited from volunteers presenting at hospitals and hospital facilities across Singapore for COVID-19 screening. After providing informed consent, the study participants will be asked to report on changes in their smell and taste sensitivity in the previous 2 weeks via a series of questionnaires; they will also be asked to prospectively track daily changes in smell and taste acuity using a self-assessment test and a series of questionnaire measures to measure the onset, severity, and recovery of changes in their chemosensory acuity for the next 28 days. A schematic of the study procedure is shown in Figure 1, and the schedule for enrolment and assessment is shown in Table 1.

**Figure 1 figure1:**
[figure not shown]
Frequency of the different test measures for the COVOSMIA-19 clinical trial. GCCRQ: Global Consortium for Chemosensory Research Questionnaire; SNOT-22: Sino-Nasal Outcome Test; SSTQ: Singapore Smell and Taste Questionnaire; SSTT: Singapore Smell and Taste Test.

**Table 1 table1:** Schedule of participant enrolment, intervention, and assessment in the COVOSMIA-19 trial.

Timepoint		Study period						
		Enrollment	In-clinic	At home (4 weeks)				Closeout
		Day 0	Day 0	Week 1	Week 2	Week 3	Week 4	Day 28
**Enrollment**								
	Eligibility screen	✓						
	Informed consent	✓						
**Procedure**								
	Questionnaires		✓					
	SSTT^a^ testing kit demonstration		✓					
	Initial SSTT session		✓					
	SSTT (daily)^b^			✓	✓	✓	✓	✓
	Additional questions (once per week)			✓	✓	✓	✓	
**Assessments**								
	Baseline variables: gender, age, education status, nationality, ethnicity, employment status, smoking status, vaping status, medication, COVID-19 test result		✓					
	Primary outcome variables: COVID-19 symptoms (and onset), smell and taste acuity			✓	✓	✓	✓	✓
	Secondary outcome variables: appetite, food enjoyment, eating behaviors, nausea, weight, food-related quality of life		✓	✓	✓	✓	✓	✓

^a^SSTT: Singapore Smell and Taste Test.

^b^Participants were asked to complete the SSTT daily from Day 1 to Day 28.

### Recruitment Procedure

Participants will be recruited from patients applying to a hospital and its ancillary units for COVID-19 screening by nasal swab polymerase chain rection (PCR) testing. Following their COVID-19 screening, individuals will be approached and invited to participate in this study and to provide informed consent.

### Inclusion Criteria for Participants

Participants are required to be aged >21 years, reside in Singapore for the next 28 days, possess a mobile device with a 3G or 4G network, and know how to use mobile apps (ie, a quick response [QR] scanner).

### Exclusion Criteria for Participants

Participants will be excluded from the study if they are unable to provide informed consent, are allergic or intolerant to any of the test items (ie, mango fragrance, jasmine fragrance, sugar, salt, coffee powder, or lime powder), are currently pregnant, or do not agree to allow the study team to access their medical records to obtain their COVID-19 infection status (ie, swab test result).

### Ethical Approval and Consent to Participate

The study (ref: 2020/00810) has been approved by the Domain Specific Review Board of the National Healthcare Group, Singapore. Written informed consent will be obtained from all eligible participants prior to entry into the study. Any adverse events or unintended effects of the study procedure will be reported to the ethics committee. This information will be given to participants both verbally and in written form (in their copy of the informed consent form) during recruitment. All data will be anonymized through the use of a unique identification number for each participant and will be stored on password-protected computers. Participants will not receive any monetary compensation for their participation in the study.

Any changes to the above protocol will be reported to the Domain Specific Review Board as appropriate. In addition, these changes will be documented on ClinicalTrials.gov. The results of this study will be disseminated through reports, publication of articles in scientific journals, publication of articles for public dissemination, and conference presentations.

### Measures

On the day of their COVID-19 swab test (Day 0), after consenting to participate in the trial, participants will complete three questionnaires to document recent changes in their smell, taste, and chemesthetic ability and to detail the frequency of a wide range of nasopharyngeal symptoms. These questionnaires include the Singapore Smell and Taste Questionnaire (SSTQ, Multimedia Appendix 1), the 22-item Sino-Nasal Outcome Test (SNOT-22) [34], and the recently developed Global Consortium for Chemosensory Research questionnaire (GCCRQ) [12]. Participants will receive the Singapore Smell and Taste Test (SSTT, Multimedia Appendix 2), a standardized home use testing kit to monitor their smell and taste acuity, and will be given a demonstration of the self-assessment procedure that they will complete daily at their place of residence for the following 28 days. All the questionnaires and instructions are available in English, Mandarin, Tamil, and Bengali, and the participants will complete all the measures via Compusense Cloud web-based data acquisition software (Compusense Inc).

### The SSTQ

Participants will complete the SSTQ (Multimedia Appendix 1) to record any recent changes in smell and taste and to describe the occurrence of sino-nasal or other COVID-19 symptoms. Participants will rate their current smell and taste sensitivity using the SSTQ (Day 0) to provide a baseline measure for their smell and taste sensitivity. This initial self-report questionnaire will quantify any recent changes in smell and taste acuity and includes questions on the participants’ basic demographics, the COVID-19–related symptoms they have experienced, the temporal onset of these symptoms, the smell and taste acuity of the participants, and their appetite-related quality of life (eg, enjoyment of food). See Multimedia Appendix 3 for information on the sources of the questionnaire items.

### The SNOT-22

The SNOT-22 will be used to quantify the presence and severity of nasal disorder symptoms [34]. Participants will be provided with a list of 22 symptoms and social and emotional consequences of nasal disorder, and they will be asked to rate the severity of each problem on a 6-point scale from “no problem” to “problem as bad as it can be.” This measure has been included to assess symptoms that are commonly associated with nasal disorders and to make a distinction between changes in smell and taste due to nasal disorders and congestion and those associated with COVID-19 infection. Current research suggests that smell and taste loss with COVID-19 infection often occurs without nasal obstruction [13,16]; therefore, we expect participants with smell and taste loss to have a differential prevalence of other common nasal disorder symptoms (eg, blocked nose).

### The GCCRQ

The GCCRQ questionnaire was developed and implemented by the Global Consortium for Chemosensory Research to assess whether and how COVID-19 infection affects sense of smell, taste, and chemesthetic sensitivity [12]. Participants are asked about their COVID-19 testing status and symptoms, and they complete 18 items relating to their sense of smell, taste, chemesthetic ability, and food flavors before, during, and after COVID-19 illness. Due to the potential for additional participant burden, the completion of this questionnaire is optional and will not affect the study participation. For participants who complete the GCCRQ, we will ascertain the extent to which the measures obtained using this approach correlate with the measures in the study.

### Daily Smell and Taste Testing

The study participants’ smell and taste acuity will be prospectively measured for up to 28 days following their clinic visit for COVID-19 testing using the home-based assessment tools detailed in this section. At the start of each daily test session, participants are to report on any changes in their smell and taste acuity by selecting either “improved,” “stayed the same,” or “worsened” before rating their current sense of smell and taste from “no sense of [smell/taste] at all” to “extremely strong sense of [smell/taste].” Participants will also be asked to “check all that apply” across a list of symptoms they have experienced in the last 24 hours from a list of COVID-19–relevant symptoms.

### The SSTT

Participants will be provided with their own standardized home-use smell and taste test that they will complete daily for up to 28 consecutive days (Multimedia Appendix 2). The questioning approach is based on that used in the Yale School of Medicine “Jiffy” Test of mell Sensitivity [35], in which respondents perform a similar procedure with Jif peanut butter.

The SSTT smell test includes two odors—a food odor (mango) and a nonfood odor (detergent)—both of which consist of odor mixtures that have been formulated by an international fragrance manufacturer (Symrise AG). The odor mixtures were chosen to avoid possible specific anosmias to individual odor compounds, and the odors are dosed at the suprathreshold level in specialized odor delivery pens (Otto Hut). Both fragrances have been tested to deliver a suprathreshold odor at a consistent intensity and stability for the duration of the home-use test period. To perform the test, the participants remove the pen lid and place the pen 3 inches from their nose while breathing normally. For each smell, participants will identify the smell and rate the perceived intensity on a visual analog scale (VAS) from “not strong at all” to “extremely strong smell.”

For the daily taste test, participants will be provided with small quantities of powder selected to represent the four prototypical tastes: “sweet” (table sugar, NTUC FairPrice), “salty” (table salt, NTUC FairPrice), “bitter” (granulated coffee powder, Nescafé), and “sour” (lime powder, Knorr). The participants will be instructed to take a small amount of each item in a sequential monadic order on the tip of their tongue with a small spoon; they will then be asked to identify and rate the perceived intensity of the taste on a VAS from “not strong at all” to “extremely strong taste” through a web-based questionnaire completed on their smartphone or other device. The participants will be asked to rinse with water between each taste stimulus and will be provided with sufficient taste stimuli for the 28 days of assessment.

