The COVOSMIA-19 study will standardize the smell and taste stimuli used by all participants to ensure consistency and provide a disposable, rapid, self-administered home use test, the Singapore Smell and Taste Test (SSTT), to minimize the risk of cross-contamination and infection spread. The trial will enable self-testing for up to 28 consecutive days and will provide a standardized longitudinal assessment of smell and taste function to enable tracking of the onset, severity, and recovery of the sensory changes reported to occur with COVID-19 infection. The standardized smell and taste test will also be compared with self-reported questionnaire measures of smell and taste changes and measured changes to sensory acuity using common household items (an approach previously used by [32]).

The primary objectives of this study are to (1) assess the prevalence of sudden changes in smell and taste sensitivity with COVID-19 infection in a population at risk for COVID-19 infection in Singapore, (2) establish the temporal onset, severity, and recovery of changes in smell and taste sensitivity with COVID-19 infection, and (3) evaluate the efficacy of the SSTT as a rapid, cost-effective, self-administered measure of changes to smell and taste compared to previous measures using household items. The secondary objective of this study is to investigate the effects of loss of smell and taste acuity on food enjoyment and appetite as well as to establish the impact of COVID-19 infection on food-related markers of quality of life. We hypothesize that loss of smell and taste acuity will be associated with COVID-19 infection, will return upon recovery from infection for the majority of patients, and will result in short-term reductions in appetite, food enjoyment, and food-related quality of life.

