### Statistical Analysis

Using a case-control study design for people testing positive (case) or negative (control) for COVID-19 infection, data will be collected on changes in smell and taste loss that have occurred in the 2 weeks prior to the COVID-19 test and on smell and taste acuity changes measured on a daily basis for up to 28 days following the COVID-19 test. The data will be used for descriptive comparisons of the onset, duration, and severity of smell and taste changes with COVID-19 infection and to report on the incidence of these changes among participants testing positive for COVID-19 infection (and those recovering from infection).

Logistic regression analysis will be used to estimate the odds ratio for loss of smell and taste sensitivity as a predictor of testing positive for COVID-19 infection. This will also enable comparison of smell and taste loss as a predictor of COVID-19 infection compared to other symptoms, such as fever and dry cough. Pearson correlations will be used to investigate relationships between smell and taste changes and other symptoms. Time-series analysis of variance (ANOVA) models will be run to investigate temporal changes in smell and taste ratings over time, with baseline ratings in smell and taste acuity corrected for at an individual level. Linear mixed models will be used to test for significant differences in smell and taste acuity between groups, with participants stratified by their COVID-19 infection status.

Factor analyses, using oblique rotation and baseline home-use test responses (conducted in-clinic), will be conducted to assess the internal consistency of our smell and taste test. Adjusted odds ratios will be calculated to investigate the best predictors of recovery of smell and taste acuity postinfection. Linear regression will be run to examine whether responses to the smell and taste test predict responses to the household item odor test (smell) and self-reported taste acuity, respectively. Regression analyses will be conducted to investigate the association between loss of smell and taste acuity and self-reported appetite and food-related quality of life. All statistical analyses will be completed using SPSS (IBM Corporation).

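### Two of the four taste stimuli (coffee and lime powder) are aromatic and no nose closure is described, so smell loss can lower the bitter and sour ratings; sugar and salt should be analysed separately

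*Protocol article*

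**What the plan says.** The Introduction makes taste a primary target alongside smell. Objective 1 covers the prevalence of change in both senses, and objective 2 is to "establish the temporal onset, severity, and recovery of changes in smell and taste sensitivity with COVID-19 infection". The Primary Outcomes section repeats onset, severity, duration and recovery for both.

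The SSTT section names one powder per taste:

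- sweet: "table sugar, NTUC FairPrice"
- salty: "table salt, NTUC FairPrice"
- bitter: "granulated coffee powder, Nescafé"
- sour: "lime powder, Knorr"

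The procedure reads: "The participants will be instructed to take a small amount of each item in a sequential monadic order on the tip of their tongue", using a small spoon. They identify each taste and rate its strength on its own visual analog scale, rinsing with water between items. Smell is tested separately with two odor pens. For the pens the article specifies normal breathing. For the powders it says nothing about the nose. The full test documents are in Multimedia Appendix 2, which is not shown.

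**The concern.** That coffee and lime powder have a distinct aroma, while sugar and salt are essentially odorless, is general knowledge and not a statement in the article. If the nose is not closed, aroma from the first two can reach the nose as they are brought to or held in the mouth. Part of the rated strength may then be smell.

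A participant with smell loss and intact taste could therefore rate coffee and lime lower, and rate them higher again as smell returns. This error is not random. It pushes toward joint loss and joint recovery, which is the pattern the study sets out to describe. It would also arise often in this population: the Introduction cites a pooled prevalence of 52.7% for olfactory dysfunction in COVID-19.

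At stake are the prevalence of taste change, its time course, and any correlation or factor structure linking the smell and taste items.

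**Working it through.** The plan states no figure on this point, so there is none to reproduce. The sample size of 235 does not enter.

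**Inputs.** Four taste items, each rated separately (The SSTT). Two are aromatic and two are not (general knowledge). The fraction f by which complete smell loss lowers the coffee and lime ratings is an assumption; the documents do not give it, so a range starting at zero is used.

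**Effect on a pooled score.** Let each item have rating r when smell and taste are intact. Under complete smell loss with intact taste, coffee and lime become r(1 − f), and sugar and salt stay at r.

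Four-item mean = [2r + 2r(1 − f)] / 4 = r(1 − f/2), so the relative fall is f/2.

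| Assumed f | Fall in coffee and lime | Fall in four-item mean | Fall in sugar and salt |
|---|---|---|---|
| 0 | 0% | 0% | 0% |
| 0.10 | 10% | 5% | 0% |
| 0.25 | 25% | 12.5% | 0% |
| 0.50 | 50% | 25% | 0% |

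If the items do not start equal, replace the one half by the share of the four-item total that comes from coffee and lime. A rule that counts taste loss when any single item falls would meet the whole of f, not half of it.

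**Do the planned analyses remove it?** Taking those in the Statistical Analysis section in turn:

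- *Individual baseline correction.* Write an aromatic item's rating as T + A·s(t), with T the taste part, A the aroma part and s(t) smell function between 0 and 1. With taste constant, the change from Day 0 is A·[s(t) − s(0)]. Correction removes T but leaves the part that moves with smell. For sugar and salt A = 0, so the change is 0. Example at f = 0.25: someone who enrols without smell rates coffee 0.75r and later r, an apparent taste recovery of 0.25/0.75 = 33% with no change in taste.
- *Factor analysis with oblique rotation.* It might show coffee and lime loading with the odor items. But it uses only the in-clinic baseline, its stated purpose is internal consistency, and no consequence for scoring is given.
- *Regression against self-reported taste acuity.* That criterion may itself mix flavor with taste, so good agreement would not expose the problem.
- *Logistic regression for a positive swab.* Prediction of infection does not require each item to be a pure measure of one sense, so this analysis is the least affected.

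The Study Limitations section notes that the SSTT gives no information near threshold and does not profile specific anosmias. It does not mention aroma in the taste items.

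**The case against.** A reader might infer that the powders are tasted with the nose open. The article does not say so. It is silent, it refers to an appendix that is not shown, and participants are given a demonstration. Step-by-step instructions are commonly left to such an appendix. If that appendix has the nose closed, the mechanism largely falls away.

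A reader might also infer that the study cannot separate taste loss from smell loss. The documents do not support that. Sugar and salt are rated individually on every test day and can be compared directly with the odor pens.

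Three further points count against a strong reading:

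- No section defines a four-item mean or a taste-loss rule that pools the four powders, and item-level scoring may sit in an analysis plan that is not shown. The f/2 figure therefore describes a score that might be used, not one that is specified.
- Participants are asked for the strength of the taste, from a small amount on the tip of the tongue. This may reduce the aroma share, though it does not remove it.
- The size of f is unknown and could be near zero.

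All of this limits the claim. It does not dispose of it: two aromatic stimuli are fixed, the described procedure contains no block on aroma, and no analysis described in the article treats the two pairs differently.

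**Conclusion.** The concern holds in a limited form. The bitter and sour ratings may carry a smell component, and any taste-loss definition or pooled score that includes them may over-count taste loss in people with smell loss and make taste recovery resemble smell recovery. Under equal starting ratings the effect on a four-item mean is f/2, from 0% at f = 0 to 25% at f = 0.50. The documents give no value of f.

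The conclusion rests on three assumptions: coffee and lime powder are aromatic as used, the nose is not closed during tasting, and taste itself is intact in the illustrated participant. It does not extend to the sweet and salty ratings, which remain a usable measure of taste apart from smell. It is a matter of analysis and interpretation, and it does not invalidate the study.

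**What to change.** In the Statistical Analysis section, prespecify that the sugar and salt ratings are analysed separately from the coffee and lime ratings. Repeat the taste-loss prevalence, time-course and smell-taste association analyses on sugar and salt alone. State that taste loss will be described as distinct from smell loss only where the sugar and salt results support it.

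The cost is a few lines of text and some extra analysis of data already collected. The downside is that the aroma-free result rests on two tastes and says nothing about loss confined to bitter or sour. For that reason the coffee and lime results should still be reported, beside the others and not discarded.

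No mid-study change to the tasting instruction is needed. Recruitment had reached 69 by October 2, 2020, and a new instruction would split a standardized test into two versions while that test is itself under evaluation.

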### Common Household Item Smell Test

For comparison with the SSTT, participants will be asked to complete a daily assessment of smell using household items (see Multimedia Appendix 2). To assess the participants’ olfactory sensitivity, we will provide them with 6 categories of common household items. Participants will be asked to choose one odor from a drop-down menu for each category and indicate their perception of it on a scale from “absent” to “heightened.” This approach is based on a previously reported self-assessment measure of smell sensitivity using household items [32], with an additional category of stimuli that are particularly high in trigeminal irritation. The items for all categories were adjusted to include culturally appropriate household items that are common in Singapore.

### Additional Questions

Once per week, participants will complete an additional set of questions (Day 7, 14, 21, and 28) relating to their enjoyment of food, appetite, weight, and food-related quality of life (eg, “I no longer enjoy cooking/preparing food”). The goal of this questionnaire is to assess the relative impact of changes in sensory acuity with self-reported appetite and food enjoyment, as it may be related to weight fluctuations observed during the period of infection.

### COVID-19 Diagnosis

During study consent, participants will provide access to the outcome of their COVID-19 diagnostic swab test, which will be associated posthoc with the unique identification number linked to the participant questionnaire and daily home-use test data.

